### Outcomes measures

#### Primary outcome measure

We hypothesize that the application of active tDCS will result in changes in the strength and variability of functional connectivity, with particular alterations in alpha (increase) and beta (decrease) frequencies, which will clinically lead to a reduction in the severity of psychopathological symptoms associated with AN, measured by the change in the EAT-26 scores between visit V1 (baseline) and V2 (end of stimulation after 3 weeks) as a primary outcome.

#### Secondary outcome measures

For the purpose of evaluating the effectiveness of tDCS in treating AN, a range of secondary outcome measures will also be utilized, defined as changes in: 1. anthropometric measurements (in this BMI), 2. brain bioelectric activity, 3. nutritional status, 4. mood, 5. neurocognitive functions (attention, memory, and some aspects of planning, verbal fluency, and another executive function), 6. psychological measurements connected with: dysfunctional metacognitive beliefs, other aspects related to thinking such as reflectivity, impulsivity, rumination, obsessive-compulsive symptoms, stress levels and assessment of early childhood injuries related to the experience of abuse, emotional, bodily, sexual, emotional, and physical neglect, and self-assessment of the appearance of one’s body, 7. selected biological markers related to stress, food intake, inflammation and neurotrophins.

As regards the neurophysiological measures, we expect that a series of the tDCS sessions will be associated with changes in three aspects: 1. reduction of lower frequencies (delta and theta) in the dominant frequency spectrogram accompanied with an increase in the power of alpha and beta frequencies, 2. modification of alpha anterior asymmetry patterns associated with affective functioning towards less right-hemisphere-oriented and more left-hemisphere oriented pattern, 3. changes in the strength and variability of functional connectivity, with particular alterations regarding alpha (increase) and beta (decrease) frequencies, what is associated with the ability to gain more relaxed and less tensive states recorded during resting-state condition. The neurophysiological examination will be conducted during the V1 and V2 meetings.

Secondary psychological outcome measures will be gathered during the initial assessment (V1) and V2, while nutritional data will be collected at V1, V2, and V3 after follow-up. Biological outcomes will be recorded at V1 and V2, with additional measurements of BMI and BIA analysis also at V3. Neurophysiological outcome measures will be obtained during V1 and V2.

### Study timeline

This study will consist of four visits:

V0: Screening visit to screen and enroll eligible patients into the study (1 to 2 days before the baseline visit).V1: Baseline visit 1 day (before intervention) to randomize patients, conduct assessments using questionnaires, perform a body composition analysis, take blood samples and perform an EEG test;V2: Visit 2, up to 3 days after the end of the intervention period, after three weeks ( ± 1 days) from baseline;V3: End of Study Visit to complete all procedures in this study, after 5 weeks ( ± 7 days) from baseline visit.

The total duration from the screening to the end of the study will be 6 weeks at maximum.

Psychological assessments: 1. Beck Depression Inventory (BDI), 2. The Children’s Depression Inventory 2 (CDI 2), 3. The Meta-Cognitions Questionnaire (MCQ-A), 4. Perceived Stress Scale (PSS-10), 5. Childhood Trauma Questionnaire (CTQ), 6. The Attention and Perceptiveness Tests version 6/9, 7. The Rey-Osterrieth complex figure test (ROCF), 8. The Yale-Brown Obsessive Compulsive Scale (CY-BOCS), 9. Color connection test (CTT-1, CTT-2), 10. The Benton Visual Retention Test (BVRT),11. The Appearance Self-Rating Sheet (ASRS),12. The Ruminance-Reflectivity Questionnaire (RRQ), 13. The Verbal Fluency Test (VFT), 14. Matching Familiar Figures Test (MFF).

Neuropsychological assessment: EEG.

Dietary behaviors and nutrition assessments: 1. Eating Attitudes Test (EAT-26), 2. Questionnaire Eating Behaviors (QEB), 3. Food Intake Variety Questionnaire (FIVq), 4. Eating Disorder Examination Questionnaire (EDE-Q 6.0).

Biological assessments: 1. Complete blood count (CBC), 2. Ferritin, 3. TSH, 4. FT3, 5. FT4, 6. Phosphorus, 7.Magnesium, 8. Calcium, 9. Cortisol, 10. Neurotrophins, 11. Leptin, 12. Visfatin.

### Sample size calculation

The number of studies that examined the effect of tDCS in patients with AN group is relatively small. To calculate the sample size, we analyzed the number of patients in the general population (patients suffering from AN in Poland) (65) and previous trials conducted by other authors (18), which reported improvement in EAT-26 scores. The statistical power was estimated at 80% to detect a difference in means of EAT-26. The baseline EAT-26 points was estimated at 72.7, with a 20-point improvement (18). To account for a dropout rate of 20%, a total of 50 individuals will be included to achieve a target number of 40 participants. Patients will be recruited for the study and randomized into two subgroups. The recruitment target was determined to ensure statistical power, which allows confirmation of the differences in the primary outcomes with an approximately 95% probability of correctly rejecting the null hypothesis. The calculation of sample size was performed using the STATISTICA software (StatSoft) and online sample size calculator (66).

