The existing literature highlights the presence of brain abnormalities in individuals with AN, particularly in specific areas such as the dorsolateral prefrontal cortex (DLPFC), cingulate cortex, and left middle occipital gyrus (9). Electroencephalographic (EEG) measurements among patients suffering from AN have shown hyperactivity of the right frontal hemisphere (10). Functional magnetic resonance imaging studies reveal diverse patterns of brain activity. Notably, when exposed to food cues, there is reported heightened activity in regions associated with reward, along with increased activation in the right DLPFC (11). These findings suggest an intensified top-down inhibition of reward processing (12). Importantly, the DLPFC is recognized for its pivotal role in cognitive control and self-regulation in dietary contexts (13), therefore, it is reasonable to question whether coupled inhibition of the right hemisphere activity can facilitate interhemispheric balance (14).

Due to the complex etiology of AN and the limited effectiveness of current therapies, coupled with a high mortality rate, there has been a search for new treatment methods. Contemporary research directions in the therapy of AN increasingly focus on neuromodulation and neurosurgery, encompassing neurosurgical ablation, deep brain stimulation, repetitive transcranial magnetic stimulation, and transcranial direct current stimulation (tDCS) (15). In our project, we formulated a hypothesis regarding the effectiveness of tDCS in the treatment of anorexia, measured as a reduction of the severity of eating disorder symptoms. At the time of writing this article, there are also four published research papers (14, 16–18) and two study protocols (19, 20) assessing the effectiveness of such therapy in AN, which encompass diverse approaches and outcomes. As of now, only one double-blind randomized controlled trial (17) has delved into the therapeutic possibilities of tDCS for AN. In this particular study, 43 participants diagnosed with AN were randomly assigned to undergo either active or sham tDCS sessions targeting the left DLPFC over ten 30-minute sessions. While the findings did not reveal significant improvements in AN psychopathology or weight recovery compared to sham tDCS, active tDCS did demonstrate a decrease in the need for excessive control over food intake and an enhancement in body image.

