Research conducted so far suggested benefits for core eating disorder symptoms of tDCS in AN. In a double-blind RCT focusing on tDCS therapeutic potential, 43 participants with AN were randomly assigned to receive active or sham tDCS over the left DLPFC during ten 30-minute sessions. While there were no significant improvements in AN psychopathology or weight recovery compared to sham, active tDCS did decrease the need for excessive control over food intake and improved body image (17). Furthermore, three smaller open-label studies (14, 16, 18) investigated the efficacy of left DLPFC anodal stimulation in AN. However, each of the studies presents a different methodology of the applied stimulation. Costanzo et al. (16) aimed to investigate tDCS’s potential in modifying inter-hemispheric balance in adolescents with AN. The study was finished by 11 patients undergoing treatment as usual (AU), with interventions comprising 18 sessions of tDCS combined with AU or family-based therapy combined with AU. No sham was used in the study. Various measures, such as EDI, EAT-26, Body Uneasiness Test (BUT), anxiety, depressive symptoms, and BMI, were employed. Medications, including aripiprazole and SSRIs, were administered, and adverse effects like itching, burning sensations, local redness, headaches, and tingling were reported. Baumann et al. (17) conducted a double-blind, randomized controlled trial with 43 inpatients to examine the effects of 10 tDCS sessions on eating behavior, body weight, and depression in AN. Participants received either active tDCS or sham tDCS. Strumila et al. (14) conducted a pilot study with nine female AN patients, assessing the effects of tDCS during 20 sessions, with two sessions per day for two weeks. Various psychiatric medications were prescribed, and measures included EDI, EDE-Q, Body Shape Questionnaire (BSQ-34), and BDI. In a study by Khedr et al. (18), anodal tDCS (2mA) for 25 minutes over the left dorsolateral prefrontal cortex daily for ten days was conducted on a group of patients. Adverse effects of tDCS were minimal, with only transient local itching reported by two patients and no other observed adverse effects. Collectively, these studies provide insights into tDCS’s potential in treating anorexia, with varying methodologies and outcomes, while indicating a generally tolerable safety profile in the context of AN treatment.

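### The stated power rests on a 20-point before-after improvement from an open-label study and describes active versus sham only if sham patients do not improve

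*Protocol article*

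**What the plan says.** The Sample size calculation section of the protocol article draws its effect from "previous trials conducted by other authors (18), which reported improvement in EAT-26 scores". It gives one effect size: "The baseline EAT-26 points was estimated at 72.7, with a 20-point improvement". On power it says: "The statistical power was estimated at 80% to detect a difference in means of EAT-26". A later sentence speaks of recruiting "with an approximately 95% probability of correctly rejecting the null hypothesis". The target is 40 evaluable participants, raised to 50 for 20% dropout. The section gives no SD, no alpha and no expected change under sham.

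The Discussion places reference 18 among "three smaller open-label studies (14, 16, 18) investigated the efficacy of left DLPFC anodal stimulation in AN" and says of its regimen that stimulation "daily for ten days was conducted on a group of patients". No comparator is mentioned for that study.

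The trial is a 1:1 randomised, double-blind comparison of active with sham tDCS, 25 per arm (Trial design; Allocation). Its primary outcome is the EAT-26 change from V1 to V2 (Primary outcome measure). The Interventions section gives treatment as usual to all patients: nutritional rehabilitation, psychotherapy, psychoeducation and, where needed, medication.

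**The concern.** An improvement from a baseline of 72.7 is a before-after change in treated patients. It contains whatever stimulation adds, together with usual care, expectancy, regression to the mean and time. The trial estimates only the first of these, because the sham arm carries the rest. Sham patients here are inpatients in a full treatment programme who attend 30 sham sessions and complete a self-report scale, so some improvement among them over three weeks is plausible.

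The only double-blind randomised trial that the article cites, in 43 participants, gives no support for a large net effect. The Background says of it: "While the findings did not reveal significant improvements in AN psychopathology or weight recovery compared to sham tDCS".

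At stake is how the result will be read. A reader told that the trial has 80% power may give a non-significant result more weight than it can bear, if the net difference worth detecting is well below 20 points.

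**Working it through.** **Inputs from the article:** 50 enrolled, 20% dropout, 1:1 allocation, effect 20 points, power 80%. **Assumed, because not stated:** two-sided alpha 0.05, a two-sample t test on EAT-26 change with equal variances, and the SD.

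**1. The article's own figure.** Dropout step: 40 / (1 − 0.20) = 50, which reproduces; 40 / 2 = 20 evaluable per arm. The base figure of 40 can be neither reproduced nor refuted without an SD and an alpha.

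**2. What SD the stated power implies.** With n = 20 per arm there are 38 degrees of freedom and the two-sided critical value is 2.024. The noncentrality is (Δ/SD) / √(2/20). Solving the noncentral t for 80% power gives Δ/SD = 0.909. If Δ = 20 is the between-arm difference, SD = 20 / 0.909 = 22.0 (22.6 by the normal approximation). Reading the sentence about 95% literally gives Δ/SD = 1.170, so SD = 20 / 1.170 = 17.1.

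**3. What the net difference is.** Net Δ = active improvement − sham improvement. If active patients improve by 20, net Δ = 20 − sham improvement. This equals 20 only when the sham improvement is zero.

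**4. Power at smaller net differences.** At SD 22 the noncentrality is 20/22 ÷ 0.316 = 2.87, 15/22 ÷ 0.316 = 2.16 and 10/22 ÷ 0.316 = 1.44. The table gives the resulting power with 20 per arm. The sham improvements of 5 and 10 points and the SDs are illustrations, not figures from the article.

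| SD of change | Net 20 (sham 0) | Net 15 (sham 5) | Net 10 (sham 10) |
|---|---|---|---|
| 15 | 98% | 87% | 54% |
| 17.1 (implied by 95%) | 95% | 77% | 44% |
| 20 | 87% | 64% | 34% |
| 22 (implied by 80%) | 80% | 56% | 29% |
| 25 | 69% | 46% | 23% |

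**5. The other reading.** Suppose the calculation was a paired before-after test. Then 80% power for 20 points would imply an SD of change of 30.3 with n = 20, or 44.0 with n = 40. The 80% would then be the chance of seeing a change within a group, and would say nothing about active versus sham. On neither reading does it describe the primary comparison with any sham improvement allowed for.

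**The case against.** The strongest reply is that the article never calls the 20 points an active-minus-sham difference and never says that sham patients stay unchanged; it speaks only of a difference in means. That is right, and a reader might go too far by saying that the authors assumed exactly zero sham change. What can be said is conditional: the stated power fits the trial's comparison only in that case, and no allowance for anything else appears. The paired reading does not rescue the claim, as step 5 shows.

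A reader might also call the source study uncontrolled. The article says open-label, and its list of open-label studies includes reference 16, which had a comparison group. The statement that no sham was used concerns reference 16, not 18. The description of reference 18 suggests a single group without proving it.

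A third tempting reading is that 20 points is an upper bound. The documents do not support this: this trial gives 30 sessions, against ten days of daily stimulation in reference 18, so a larger effect cannot be excluded.

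The sham-controlled trial must be cited fairly. It also used ten sessions, and the article reports that active stimulation lessened the need for excessive control over food intake and improved body image. Its non-significance in 43 patients does not show that there is no effect.

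Finally, the power figures depend on unknowns. If the SD were 15, a 5-point sham improvement would leave power at 87%, above the stated 80%. This objection stands, and is why the table shows a range.

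**Conclusion.** The point holds in this form: the stated power is built on a within-group improvement from an open-label study, and it applies to the active-versus-sham comparison only if none of that improvement would also occur under sham. At the SD that makes the 80% true, 5 points of sham improvement reduce power to 56% and 10 points to 29%. Across SD 15 to 25 the figures are about 87% to 46% and 54% to 23%. All of this assumes two-sided 5%, 20 evaluable per arm and a t test on change.

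A reader might infer that 50 patients are too few. That does not follow: without an SD and an expected sham change, no corrected sample size can be derived. What fails is the justification of the power claim. Randomisation, the primary endpoint and the type I error are untouched. That the 80% and the approximately 95% disagree is a separate defect in the same section.

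**What to change.** Restate the Sample size calculation section in between-arm terms, for example: *With 20 evaluable participants per arm and two-sided alpha 0.05, the trial has 80% power for an active-minus-sham difference of 0.91 SD in EAT-26 change.* State the SD used and its source. Add that the 20 points is a within-group improvement reported by an open-label study and is not an estimate of the difference from sham. Do not describe it as an upper bound.

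Give power at net differences of 20, 15 and 10 points for the SD chosen. If the SD remains uncertain, show a range such as 15 to 25 and label it illustrative.

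The cost is a few sentences and a short table. Enrolment, treatment and procedures stay as they are. The downside is a less favourable stated power.

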### Allocation

The patients included in the study will be randomly assigned to one of two subgroups, independently of examined variables, during the entry of the study: Active group - AG (tDCS group, n=25) and Sham group - SG (placebo group, n=25).

Eligible patients will be randomized in equal proportions between the AG and SG arm. A random sequence generator (Urbaniak GC, Plous S. Research Randomizer (Version 4.0) 2013) will be used to randomize active versus sham arms. The allocation to study groups will be performed by a researcher not involved in the stimulation and assessment of patients.

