### Statistical methods

The statistical analysis will be performed by the Statistica package, version 13.0 (StatSoft, TIBCO Software Inc.). Before analysis, the Shapiro-Wilk test will be applied to examine the distribution of examined variables where normality will be assumed if p > 0.05. The chi-square test will be used to calculate differences in the qualitative data at baseline between groups. Depending on data distributions, the between-group comparisons will be performed using the ANOVA or Kruskal-Wallis rank-based nonparametric test for quantitative outcomes. To compare groups between baseline and endpoint assessments and follow-up assessments, repeated measures of ANOVA or aligned rank-transform ANOVA and McNemar’s test will be conducted. All analyses will be performed according to the ICH E9 Statistical Principles for Clinical Trials (67). Bonferroni correction of obtained significance levels will be used to correct for multiple comparisons. The additional characteristics of the participants and dropouts will be performed for an additional assessment of possible non-random differences.

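### The sample-size section gives two incompatible powers for the EAT-26 comparison, 80% and about 95%, and does not show which one applies

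*Protocol article*

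**What the plan says.** All the power statements are in one paragraph of the protocol article, under Sample size calculation.

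- First power: "The statistical power was estimated at 80% to detect a difference in means of EAT-26".
- Effect: "The baseline EAT-26 points was estimated at 72.7, with a 20-point improvement (18"). The paragraph does not say whether the 20 points are a change within an arm or a difference between active and sham.
- Size: "To account for a dropout rate of 20%, a total of 50 individuals will be included to achieve a target number of 40 participants". The Allocation section adds "Eligible patients will be randomized in equal proportions between the AG and SG arm", so about 20 evaluable per arm.
- Second power: "The recruitment target was determined to ensure statistical power, which allows confirmation of the differences in the primary outcomes", followed directly by "with an approximately 95% probability of correctly rejecting the null hypothesis".
- Other input: "To calculate the sample size, we analyzed the number of patients in the general population", which the text identifies as patients with anorexia nervosa in Poland, alongside earlier trials.

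The paragraph gives no SD, significance level or sidedness. The Statistical methods section mentions significance levels only in this sentence: "Bonferroni correction of obtained significance levels will be used to correct for multiple comparisons".

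**The concern.** The probability of correctly rejecting the null hypothesis is power. The paragraph therefore gives two values for one quantity. It offers no second sample size, effect, endpoint or test to which the second value could belong: there is one primary outcome, one 20-point figure, one dropout rate and one recruitment target.

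The figure affects how a non-significant result is read. At 95% power the risk of missing the assumed effect is 5%; at 80% it is 20%, four times as large. A null result is a realistic possibility here: the Introduction reports that the one earlier double-blind randomised trial found no significant improvement in psychopathology over sham. A reader who relies on the 95% would take a null result as much stronger evidence against the assumed effect than the 80% supports.

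The national patient count adds to the difficulty. The number of patients in a country plays no part in the power of a two-arm comparison of means, so listing it as an input makes it harder to see what was calculated.

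**Working it through.** **Inputs from the protocol article.** Difference 20 points; 40 evaluable of 50 enrolled; dropout 20%; 1:1 allocation, so n = 20 evaluable or 25 enrolled per arm; power 80% and about 95%.

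**Assumed, because not stated.** Two-sided α = 0.05, with one-sided 0.05 also tried; a two-sample t comparison; the 20 points taken as a between-arm difference. The SD is solved for.

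**Step 1. The article's own figure.** 40 / (1 − 0.20) = 50. This reproduces. Neither power can be reproduced without an SD and α.

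**Step 2. What each power requires at 20 per arm.** Power = P(|T| > t_crit), where T is noncentral t with 2n − 2 = 38 degrees of freedom and noncentrality d√(n/2) = d√10, and t_crit = 2.024. Solving for d, with SD = 20/d:

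| Power | d | SD for 20 points |
|---|---|---|
| 80% | 0.909 | 20 / 0.909 = 22.0 |
| 95% | 1.170 | 20 / 1.170 = 17.1 |

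The normal approximation, d = (1.960 + z_power)√(2/20), gives 0.886 (SD 22.6) and 1.140 (SD 17.5). The two powers therefore imply two different SDs.

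**Step 3. Power at 20 per arm over a range of SDs, for a 20-point difference.**

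| SD | 15 | 17 | 20 | 22 | 25 | 30 |
|---|---|---|---|---|---|---|
| Power | 98% | 95% | 87% | 80% | 69% | 54% |

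The documents do not fix a column.

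**Step 4. Can some reading give both figures?** Start from d = 0.909, which gives 80% at 20 per arm, two-sided.

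- Count all 50 enrolled (25 per arm, no dropout): 88%.
- Use a one-sided 5% test at 20 per arm: 88%.
- Do both at once: 94%. This needs two unstated changes, and zero dropout contradicts the 20% in the same paragraph.
- Keep n and d and relax α: a two-sided level of about 0.23 would be needed to reach 95%.
- Reverse direction, 95% at 25 per arm (d = 1.041): power at 20 per arm is 89%, not 80%.

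**Step 5. The gap in patients.** If 20 per arm give 80%, then 95% needs 33 per arm (94.7% at 32, 95.3% at 33). That is 66 evaluable and 66 / 0.8 = 82.5, so 83 enrolled. The normal approximation gives 34 per arm, 68 evaluable and 85 enrolled. If instead 20 per arm give 95%, then 13 per arm (26 evaluable) would already give 80%.

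**The case against.** The strongest reply is that the 95% is a slip of wording: a 95% confidence level, meaning α = 0.05, described as if it were power. The 80%, the 40 evaluable and the 50 enrolled would then all stand. This is plausible and cannot be excluded, but the article does not say so, and the sentence would still need correcting.

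A second reply is that the 95% is attached to the recruitment target and not expressly to the 40 evaluable patients, and that 80% could be a planning minimum with 95% the power reached. The first part is true of the text but does not help, since the figures conflict at 40 and at 50. The second is arithmetically possible with an SD of about 17, where 26 evaluable would give 80%. No such smaller number appears, and the article presents 40 as the target.

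Two stronger readings are tempting. A reader might infer that the power of the primary comparison has been shown to be wrong, or that the trial is too small and needs 83 patients. The documents support neither: without an SD and α the 80% may be correct, and the larger number applies only if 95% was truly intended and 40 evaluable give 80%. A reader might also infer from the national patient count that a survey-precision calculator was used. That is a guess about a calculation that is not shown.

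A condensed article may leave the SD and α to a fuller protocol, so their absence alone is not the point. It matters because the conflict cannot be resolved without them.

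**Conclusion.** The point holds as an inconsistency. The section gives two values for the power of the primary EAT-26 comparison that cannot both be true under one set of inputs, and a figure on which the trial's size is justified is therefore misstated in at least one place. The stated risk of missing the assumed effect is either 20% or 5%. In standardised terms the gap is 0.91 against 1.17.

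These sizes rest on an assumed two-sided 5% level, a two-sample t comparison and 20 evaluable per arm. The incompatibility does not depend on the SD, and it survives a change to 25 per arm or to a one-sided test. Which figure is right remains open.

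The SDs of 22 and 17 are back-calculated from the stated powers and are not evidence about EAT-26. The 20 points need the same caution: they are given only as an improvement taken from an earlier study that the Discussion lists among open-label studies, not as an active-minus-sham difference.

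**What to change.** 1. State one power only, for 20 evaluable patients per arm, computed from the α, sidedness, SD and active-minus-sham difference actually used, and give those inputs.
2. Delete the 95% sentence, or rewrite it as a significance level if that was meant.
3. Do not present the national number of patients as an input to the power calculation. It can stay as background on recruitment.
4. If the inputs cannot be recovered, report the detectable standardised difference instead: about 0.91 SD at 80% power, two-sided 0.05, 20 per arm. Do not convert it to 20 points by claiming an SD of 22, because that SD comes from assuming the 80% and would be circular.

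Keep 50 enrolled for 40 evaluable. The change is to wording only: no patients, visits or analyses are added. The one drawback is that the stated power may become less favourable.
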